##### Short form 36 version 2 (SF-36v2)

The SF-36v2 [47] is a widely used health status questionnaire comprising 36 items which are organized into 8 subscales (Physical Functioning, Role Physical, Bodily Pain, General Health, Vitality, Social Functioning, Role Emotion and Mental Health) from which the Physical and Mental component scales are derived.

##### Memory complaint questionnaire (MAC-Q)

The MAC-Q is a six-item scale of self-reported memory decline in which participants compare current memory ability with past performance for given situations [48]. Scores range from 7 to 35 with higher scores considered to reflect perceived cognitive decline.

##### Hospital anxiety and depression scale (HADS)

The HADS is a 14-item self-rating instrument designed to assess the presence and severity of anxiety and depressive symptoms in medical patients within hospital out-patient, primary-care, and community settings for all age groups [49]. The scale consists of separate seven-item subscales for depression and anxiety.

##### Delis-Kaplan executive function system (D-KEFS) - verbal fluency

The D-KEFS verbal fluency task assesses the participant’s ability to produce verbal responses in accordance with set rules in the time period of 1-min [50]. Letter fluency taps into task initiation, simultaneous processing, systematic retrieval of responses and processing speed. Category fluency requires the same skills as letter fluency, but uses an over learned semantic category as the singular rule (verbal administration only).

##### Stroop task

This test measures cognitive flexibility, gauged by the participant’s effectiveness in processing stimuli as task demands increase over 3 successive trials [51].

##### Digit symbol coding

This subtest of the Wechsler Adult Intelligence Scale (3rd edition) (WAIS–III) [52] measures attention, visual scanning, working memory and speed of information processing.

##### Digit span (forward and backwards)

This WAIS–III subtest [52] will be used to measure attention and working memory.

##### Cambridge contextual reading test (CCRT)

The CCRT [53] sets the National Adult Reading Test (NART) words within semantic and syntactic context, and provides a predicted measure of verbal intelligence.

##### NEO five-factor inventory (NEO-FFI)

This is a 60-item version of the NEO-personality inventory (version 3) that provides a quick, reliable, and accurate measure of the five domains of personality (Neuroticism, Extraversion, Openness, Agreeableness, and Conscientiousness) [54].

##### Attitudes to ageing questionnaire

This is a 24-item cross-cultural attitudes to ageing questionnaire which asks about psychological growth, psychosocial loss and physical changes [55].

#### Physical activity assessment

##### Physical activity measurement

*7-Day Pedometer Recording:* Pedometers will be used to provide an objective measure of PA. Change in steps per day is the primary outcome measure of this study. Participants will be provided with a pedometer (Yamax CW-700/701 Digi-walker, Yamax Co., Japan), and asked to keep to their usual activities and to wear it for five weekdays and the weekend, during the week following the baseline visit. Participants will be instructed on how and when to wear the device, how to record their steps and how much time they spent sitting each day in a 7-day diary. Any time the pedometer is not worn will be recorded and all activities done during this time recorded. The pedometer and diary are posted back to the research team after the measurement period. This measurement will be repeated at follow-up visits.

##### Physical activity questionnaires

*CHAMPS physical activity questionnaire for older adults*: This PA questionnaire, designed for older adults, collects information on various PA, their frequency and duration [28].

*Stage of Change Instrument (SOC)*: The participant’s current stage of PA behavior will be assessed using the SOC [29]. Amount and frequency per week of moderate and vigorous intensity leisure activity will be recorded and used as a measure of moderate and vigorous physical activity (MVPA).

*Self-efficacy Questionnaires:* PA self-efficacy under adverse events (SEQ) will be assessed with a 5-item questionnaire [30]. Program specific PA self-efficacy (PASSE) will be measured using the approach of Ewart and Taylor (1985) [31] where participants rate on a scale of 0–100% their confidence to complete a specific PA task.

#### Functional fitness assessment

Functional fitness will be assessed with a battery of tests briefly outlined below and previously described [56, 57].

*Grip strength*: Measured on both hands with a Smedleys hand dynamometer [58].

*Step Test:* This test assesses dynamic balance. The participant will step one foot on then off a 7.5 cm high step as many times as possible in 15 s without using hand support [59].

*Sit-to-Stand Test*: A test of functional lower limb strength. The participant is seated in a standard chair and stands up and down 5 times as quickly as possible while being timed [60].

*Timed Up and Go Test (TUG):* TUG assesses agility and leg strength. The participant is timed whilst standing up from a standard chair, walking three meters and then returning to sit again in the chair [61].

*6-min Walk Test:* The participant walks as far as possible around a standardized course in 6 min to assess cardiovascular fitness [62]. Heart rate is recorded every minute, peak heart rate determined (Polar FS3c Heart Rate Monitor, Polar Electro Oy, Kempele, Finland) and rate of perceived exertion (RPE) measured at the end of the test [63].

#### Goal identification interview

The Bangor Goal-Setting Interview (BGSI) was developed by Clare & Nelis (2012) [17] to identify goals for goal oriented programs for behavior change in PA and cognitive activity and was based on the Canadian Occupational Performance Measure (COPM) [64]. The interview was adapted for use in the INDIGO study to specifically focus on goals for physical activity. The BGSI will be used to identify PA goals and as an outcome measure of performance and level of satisfaction with current performance. Participants will be asked to discuss the four areas of physical health (PH), physical activity (PA), physical function (PF) and every day function (EDF) and identify any issues that might form the basis of goals. They will rate the importance of and readiness to change in the 2 areas of PF and PA on a scale of 1–10. They will be asked to identify 3–5 goals in the area of PF (e.g., strength, agility, fitness etc.) and PA (type, frequency, duration etc.). The participant will rate the performance and satisfaction for each goal on a scale of 1–10. These goals will be assessed again at the follow-up visits. The use of this new interview will enable us to focus the goal orientation around PA as a motivation for increasing PA in this population.

### Apolipoprotein (APOE) genotyping

As we and others have shown that the APOE genotype can interact with PA outcomes [12, 65] the APOE genotype will be adjusted for in the final analysis. A saliva sample for DNA will be collected at baseline using a Oragene DNA Self-Collection kit (Oragene DNA (OG-500) DNA Genotek Inc., Ontario, Canada). Determination of APOE genotype will be performed centrally at the Biochemistry Department at Royal Perth Hospital, Western Australia, using the method of Hixon and Vrernier (1990) [66]. All samples will be batched and processed once the final baseline assessment has been completed.

### Follow-up assessments

Participants will be contacted 6 and 12 months after baseline. All the cognitive and physical assessments from baseline will be repeated except for the collection of saliva for APOE.

### Program and process evaluation

After 6 and 12 months, participants will be asked to complete questionnaires to give feedback on the program. All participants will receive feedback on their results after their 12 months assessment.

### Randomization and blinding of participants

After the baseline visit participants will be randomised to a goal setting and mentoring intervention group (GM-PA) or control group (CO-PA) according to a list of computer-generated random numbers in varying block sizes using the “ralloc” user-written command implemented in Stata 12 statistical software [32]. This will be done by an investigator not involved with the data collection or intervention and concealed from the study personnel. The research assistants responsible for the cognitive and clinical assessment will be blinded to treatment allocation (single blind). Participants in the intervention group and the control group will have the same number of face-to-face and telephone contacts. The RCT will be a 6 month intervention followed by a further 6-months of continued PA but without further structured encouragement. We have selected this timeframe as we have previously demonstrated that cognitive and health benefits from this level of PA are evident after 6 months [12, 67]. Follow-up after a further 6 months will allow us to examine long term effects of the intervention.

### The physical activity intervention

Given that PA has been found to be beneficial [12] and that everyone should be encouraged to engage in regular PA both groups (GM-PA, CO-PA) will receive the same PA program, an additional 150 min of moderate intensity PA/week. The program is progressive in duration and intensity taking 8 weeks to reach moderate intensity (55–65% heart rate reserve) for each individual. Participants will be asked to complete the PA as 3 × 50-min sessions a week or 5 × 30-min sessions a week. Intensity will be monitored using the Borg Perceived Rate of Exertion scale (RPE 10–12) [63]. They will be encouraged to (although not limited to) complete this as walking to maximise the opportunities for each person to be able to participate within their physical ability, at no financial cost and to reach the target of moderate intensity.

Participants will receive a manual including the same information about progressive walking, water walking, swimming and cycling programs and exercise safety [13]. The PA program will be outlined by a trained facilitator as part of a baseline workshop. They will explain the activities, their frequency, intensity and how to record details in standardised PA diaries. PA diaries will be returned monthly in prepaid envelopes. Participants will receive a report on their PA and fitness at 6 months. They will be asked to continue PA for another 6 months without any contact.

### PA adherence

Adherence to the prescribed PA will be assessed from self-reported PA diaries: type, frequency, duration and intensity of the PA will be determined from these records. Adherence will be calculated as the number of minutes of moderate activity completed relative to the prescribed 150 min/week expressed as a percentage.

### Goal orientation intervention group (GM-PA)

The objective of Goal Orientation program (GO) is to the enhance PA self-efficacy and increase PA. It will be developed from 2 sources. The first is a behavioural intervention package which we previously developed based on the Stages of Change Model and Bandura’s Social Cognitive theory [68]. The package matched to the PA stage of change of the participant focused on the development of self-efficacy using amongst other strategies identification of PA goals and setting short and long-term goals. This approach will be modified to focus on goal orientation and the goal setting techniques described below. Secondly, the goal orientation approach developed by Clare and colleagues [15, 69, 70] and used to improve everyday functioning in early stage AD will be modified for participants with SMC and MCI and used as the basis for the proposed GO intervention. This program will incorporate individual goal identification, goal setting and the development of strategies, practical aids and action plans for goal attainment. The participant’s 5 individual goals will be identified at baseline using the PA and PF information from the BGSI. Participants will be asked to select 3 personal goals from these areas. Examples of these goals could include: increasing PA; getting fitter; improving strength, mobility or balance; or feeling better. These 3 goals will be operationalised and worked on during the intervention period and will be the focus of the GO program.

Participants will receive a resource manual the content of which will be delivered via workshops facilitated by trained research staff and supported by the mentoring program.

### Control group (CO-PA)

In addition to the PA program participants in this group will receive a standard education program including healthy ageing, dealing with stress and depression and enjoying retirement delivered via a resource manual and workshops. They will also receive the standard telephone contact support (described above) during which the volunteer peer-contact (PAL) will follow a script and record progress but not give any feedback or motivational advice.

### Workshop content and delivery

In the first 6 months 3 group-workshops will be conducted for both groups. The first will have a duration of two hours: the first hour will be the same for both groups outlining the PA program, safety, the use of the educational materials, how to record the frequency and intensity of their PA, and the workshop and telephone call schedules and will include a walk session. The GM-PA second hour will focus on identifying specific PA goals, operational goals and strategies that will be employed to attain these goals. For CO-PA the content will be a general health/education topic. The remaining workshops will be of 1-h duration at 8-weekly intervals. GM-PA workshop topics will include: setting SMART goals; evaluating progress; feedback; getting the most out of mentoring; identifying barriers to goal attainment; developing practical aids to overcome specific barriers; reassessment of goals; identification of effective and ineffective strategies and review of the action plan. Participants will be asked to work on the goals, utilise strategies and implement the action plan individually as well as with their mentor in between the workshop sessions. These strategies meet the recommendations for best practice for the maintenance of PA in the long-term [71]. Workshop topics for the CO-PA group include; healthy ageing, stress anxiety and depression, and enjoying retirement. The workshops for the two groups will be held at different times to avoid contamination between the two groups.

### Health economic analysis

Health economic modeling will be employed to estimate the potential cost-effectiveness of GM-PA. Decision analysis [72] will be used to compare the downstream consequences of GM-PA versus CO-PA. The incorporation of Markov [73] and life-tabling [74] techniques will allow for the modelling of outcomes beyond the 12-month duration of the study. The main output of interest is incremental cost-effectiveness ratios in terms of net costs per unit of health gain. Net costs will comprise the costs of GM-PA minus costs saved from the reduction in downstream health services utilization. Health gains will be measured in a variety of ways. Years of life gained and quality-adjusted life years (QALYs) gained will be estimated, both enabled by the collection of time-to-outcome data and quality of life data, as described above. All health economic analyses will be undertaken in accordance with recommended approaches, such as 5% discounting of estimated future costs and health gains. To account for any uncertainty in the data inputs for health economic modeling, sensitivity and uncertainty analyses will be undertaken via Monte Carlo simulation [75].

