##### PALS training course

Volunteers randomized to the role of PALS will attend a 3-h training course on how to deliver the standard telephone contact to the CO-PA group and their reporting responsibilities. They will have a script to follow and will only ask participants to report the PA program they have been given. PALS will be directed not to engage the participants in any motivational talk about their PA.

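### The written definition of net cost leaves out the cost of delivering CO-PA, so taken literally it overstates the incremental cost of GM-PA over its named comparator

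*Protocol article*

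**What the plan says.** Three consecutive statements in the Health economic analysis section of the protocol article matter here.

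- The comparison: "Decision analysis [72] will be used to compare the downstream consequences of GM-PA versus CO-PA".
- The output: "The main output of interest is incremental cost-effectiveness ratios in terms of net costs per unit of health gain".
- The numerator of that output: "Net costs will comprise the costs of GM-PA minus costs saved from the reduction in downstream health services utilization".

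Other sections show what CO-PA consists of. Under Randomization and blinding of participants, the two groups "will have the same number of face-to-face and telephone contacts". Under Control group (CO-PA), participants, in addition to the PA program, "receive a standard education program including healthy ageing, dealing with stress and depression and enjoying retirement delivered via a resource manual and workshops". Under PALS training course: "Volunteers randomized to the role of PALS will attend a 3-h training course". The sections on the physical activity intervention, PALS telephone contact, workshop content, and mentor and PAL support add that the PA program is common to both arms, that PALs call on the same schedule as mentors, that both arms have three workshops, and that both sets of volunteers have a senior support person from the research team.

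**The concern.** An incremental ratio needs the numerator and the denominator to be differences between the same two options. Here the health gain and the downstream savings are differences between GM-PA and CO-PA, but the programme cost, as worded, belongs to GM-PA alone. The numerator therefore combines one arm's total with a between-arm difference.

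Because CO-PA costs something to deliver, the literal definition makes GM-PA look more expensive relative to CO-PA than it is. With a positive health gain, the ICER is too high. A programme that is good value against its comparator could be reported as poor value. Whether the program is cost effective is one of the questions listed in the Background, and the Discussion anticipates a cost-effective strategy that can be put into practice.

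**Working it through.** The article gives no cost, saving or ICER, so there is no figure to reproduce. The check is algebraic, followed by an illustration on assumed values.

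**Notation.** C_GM and C_CO are the programme costs. D_GM and D_CO are the downstream health-service costs. S = D_CO − D_GM is the downstream saving from GM-PA relative to CO-PA.

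**Step 1: incremental cost for the stated comparison.**
(C_GM + D_GM) − (C_CO + D_CO) = C_GM − C_CO − S.

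**Step 2: net cost as the article defines it.**
C_GM − S.

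**Step 3: the difference.**
(C_GM − S) − (C_GM − C_CO − S) = C_CO.

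The excess equals the CO-PA programme cost, whatever the value of S. It is positive whenever CO-PA costs anything.

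**Step 4: is C_CO more than trivial?** These are the resources described for each arm:

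| Item | GM-PA | CO-PA |
|---|---|---|
| PA program, manual, monthly diaries | yes | the same |
| Workshops | 3 (2 h, 1 h, 1 h) | 3 (2 h, 1 h, 1 h) |
| Telephone calls | 6 | 6, same schedule |
| Volunteer training course | 8 h | 3 h |
| Senior support person | yes | yes |
| Arm-specific content | goal-setting manual and workshops | education manual and workshops |

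The shared items would largely cancel in a true increment. In the written definition they do not. The training hours differ, so the two programmes need not cost the same.

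**Step 5: illustration (assumed values, not in the article).** Set C_GM = 1, C_CO = f and S = s. The written numerator divided by the true increment is (1 − s) / (1 − f − s).

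| f = C_CO/C_GM | s = 0 | s = 0.10 |
|---|---|---|
| 0.25 | 1/0.75 = 1.33 | 0.90/0.65 = 1.38 |
| 0.50 | 1/0.50 = 2 | 0.90/0.40 = 2.25 |
| 0.75 | 1/0.25 = 4 | 0.90/0.15 = 6 |

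For a given positive health gain, the ICER is inflated by the same factor. The factor depends heavily on both assumed values. It loses meaning when C_CO is close to C_GM: at f = 0.90 and s = 0.10 the true increment is zero, and no ratio exists.

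**The case against.** The strongest reply is that the sentence is shorthand. It follows two statements that fix a comparison with CO-PA and an incremental ratio, and the section says that the analyses will follow recommended approaches. An incremental ratio against a named comparator subtracts the comparator's cost by definition. The article never says full or gross cost. This stands as evidence of probable intent, and it is why the overstatement must be tied to a literal reading. It does not remove the point, because the sentence lists what net costs consist of and the comparator's cost is not listed. The only recommended approach given as an example is discounting.

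A second reply is that an article condenses a fuller plan, and that Table 2 gives a Health Economics questionnaire to all participants at 0, 24 and 48 weeks. Costing detail may indeed be elsewhere, and nothing says that CO-PA costs will go unrecorded. But the point concerns a definition that is stated and does not match its own comparator, not an absent detail. The content of the questionnaire is not shown, so it cannot settle whether programme delivery costs are captured.

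A third reply is that CO-PA may be a trial-only attention control with no cost in practice. The article does not say so. If no programme were the real comparator, health gains measured against CO-PA would not match it either.

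Finally, cost-effectiveness is the last of five Background questions and is not among the primary or secondary aims stated there. With a positive health gain, the error runs against GM-PA, so it would not produce a false claim of good value. Both are fair and limit the importance of the point.

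**Conclusion.** The point holds as an error in a stated definition. Taken literally, the net cost exceeds the incremental cost of GM-PA over CO-PA by exactly the CO-PA programme cost. The direction is certain provided CO-PA has some delivery cost, which its description supports. The size is not known: the factors of 1.33, 2 and 4 rest on assumed cost shares of 25%, 50% and 75% and on zero downstream savings. The primary steps/day analysis is unaffected.

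Three stronger readings should be resisted:

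- A reader might infer from the equal contact numbers that CO-PA costs nearly as much as GM-PA, and hence that the numerator is inflated up to tenfold (1/(1 − 0.90) = 10). The article has no cost data to support this, and the 3-h and 8-h training courses point to some difference between the arms.
- A reader might infer that the authors have decided to ignore CO-PA costs. The incremental framing suggests otherwise.
- A reader might infer from "both enabled by the collection of time-to-outcome data and quality of life data, as described above" that the trial has no source for such data, since no outcome is labelled time-to-event. That goes too far. Participants keep a record of illness, medications, injury and falls, and the content of the Health Economics questionnaire is not shown.

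**What to change.** Replace the net-cost sentence with a definition that matches the comparator:

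net cost = (GM-PA programme cost − CO-PA programme cost) − (downstream health-service costs saved relative to CO-PA).

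State that CO-PA delivery resources (PAL training, workshops, manual, call support, staff time) will be recorded alongside those of GM-PA and valued in the same way. If a comparison of GM-PA with no programme is also wanted, present it separately, with health gains estimated against no programme.

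The cost is one or two sentences, plus a tally of CO-PA delivery resources if none is being kept. The tally is easiest to collect while the programmes are running. No change to the design, sample size or primary analysis is needed.
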